### Participants

#### Sample size calculation.

Given that the hypotheses in this study involve both between-subjects comparisons (intervention vs. control groups) and within-subjects measurements across three time points, the sample size was calculated using the *“ANOVA: Repeated measures, within-between interaction”* option in G*Power 3.1 software. Based on an expected medium effect size (f = 0.25), an alpha level of 0.05, and a desired statistical power of 0.80, the required sample size was determined to be 28 participants per group. The choice of f = 0.25 was informed by Cohen’s conventional benchmarks and supported by findings from related educational and exergaming interventions. For instance, Zhao et al. [21] conducted a meta-analysis of 16 randomized controlled trials involving 2,962 students and found that exergames significantly improved PE learning outcomes, with a standardized mean difference (SMD) of 0.45, which corresponds to a medium effect size. Given the educational nature of our intervention and the exploratory context, this estimate was considered both conservative and realistic. To account for an anticipated dropout rate of 20%, the target sample size was increased to 35 participants per group, resulting in a minimum total of 70 participants. To ensure sufficient power and account for unforeseen attrition, more participants than the minimum required will be recruited.

Since this study employs a cluster randomized controlled trial design, it is essential to account for the intra-cluster correlation (ICC) to avoid underestimating the required sample size. Participants within the same class may exhibit correlated outcomes due to shared learning environments and peer interactions. To adjust for clustering, we applied the design effect formula:

Design Effect=1+(m−1)×ICC

Where:

*m* = average cluster size (22 students per class)*ICC* = assumed intra-cluster correlation (conservatively estimated at **0.02** based on similar educational interventions)

Thus:

Design Effect=1+(22−1)×0.02=1+21×0.02=1.42

The adjusted sample size becomes:

70×1.42≈100 participants

To ensure adequate power and account for potential attrition and clustering effects, we plan to recruit 176 participants across 8 classes, which exceeds the adjusted minimum requirement.

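### An SMD of 0.45 does not support an interaction effect size of f = 0.25, and the sizing makes no degrees-of-freedom allowance for 4 v 4 classes

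*Protocol article*

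**What the plan says.** All of this is in the protocol article, Sample size calculation. The method is stated as: "the sample size was calculated using the *“ANOVA: Repeated measures, within-between interaction”* option in G*Power 3.1 software". The inputs are "Based on an expected medium effect size (f = 0.25"), "an alpha level of 0.05" and "a desired statistical power of 0.80", giving 28 per group. The value of f is attributed to Cohen's benchmarks and to related interventions, the example being a meta-analysis which, it says, "found that exergames significantly improved PE learning outcomes, with a standardized mean difference (SMD) of 0.45, which corresponds to a medium effect size". The text concludes that "this estimate was considered both conservative and realistic".

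Dropout of 20% raises 28 to 35 per group, 70 in total. A design effect of 1.42 (22 per class, ICC 0.02) raises 70 to about 100. The section ends: "we plan to recruit 176 participants across 8 classes, which exceeds the adjusted minimum requirement". Study design allocates four classes to each arm, and Data analysis plans mixed models with class random effects.

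**The concern.** Cohen's medium label sits on different scales for an SMD and for an interaction f, so sharing the word does not make 0.45 and 0.25 the same effect. No conversion is shown. If the SMD is the evidence for f, a reader will take the trial to be comfortably powered for an effect of that size, which the section does not demonstrate.

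Separately, a design effect inflates the variance but leaves the test with individual-level degrees of freedom. With eight randomised classes, the between-arm comparison has about 6 df, and the loss of power is not trivial. At stake is how a null result is read: as informative about 0.45 SD, or not.

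**Working it through.** **1. The protocol's own figures.** For the G*Power interaction test, λ = 3·N·f²/(1 − r), with 2 and 2(N − 2) df, where N is the total and r the correlation between visits.

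- At f = 0.25 and the default r = 0.5, N = 28 in total gives power 0.81. Twenty-eight per group (N = 56) gives 0.99.
- At r = 0, N = 54 (27 per group) gives 0.81. The protocol does not state r, so 28 per group is not reproduced at the default. If it is a total misread as a per-group figure, the error is on the safe side for f = 0.25.
- The later steps reproduce: 28/0.8 = 35; 1 + 21 × 0.02 = 1.42; 70 × 1.42 = 99.4.

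**2. Converting SMD 0.45.**

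- Two-group effect: f = d/2 = 0.225, below 0.25.
- Interaction with group differences 0, d, d over the three visits: the mean difference is 2d/3 and the deviations are −2d/3, d/3, d/3, with mean square 2d²/9. Each arm carries half, so f = (d/2)√(2/9) = 0.2357d.
- At d = 0.45, f = 0.106. For f = 0.25, d = 0.25/0.2357 = 1.06 SD at both later visits.

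**3. The interaction calculation at f = 0.106.**

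- r = 0.5: 146 in total; 146/0.8 = 182.5; × 1.42 = 259.
- r = 0.7 (assumed): 88 in total; 88/0.8 = 110; × 1.42 = 156.

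The planned 176 lies between the two. These chains start from a total as the formula gives it, whereas the protocol's chain starts from 28 per group, so 259 and 100 are not like for like.

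**4. Power for 0.45 SD with class-level df.** Four classes per arm and 22 × 0.8 = 17.6 analysed per class give a variance inflation of 1 + 16.6 × 0.02 = 1.332. SE = √(2v × 1.332/70.4) = 0.1945√v, where v is the variance of the contrast in SD² units. The test is a noncentral t on 8 − 2 = 6 df, critical value 2.45. I assume equal correlation r between all visits and the same ICC for every contrast. For one later visit, v = 2(1 − r) as a change score and 1 − r² baseline-adjusted. For the mean of both later visits, v = (1 + r)/2 + 1 − 2r and (1 + r)/2 − r². On 6 df, 80% power needs a difference of 3.37 × SE.

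| Contrast | r | v | SE | Power | Detectable at 80% (SD) |
|---|---|---|---|---|---|
| One visit, change | 0.5 | 1.00 | 0.195 | 49% | 0.66 |
| One visit, adjusted | 0.5 | 0.75 | 0.169 | 61% | 0.57 |
| Both visits, change | 0.5 | 0.75 | 0.169 | 61% | 0.57 |
| Both visits, adjusted | 0.5 | 0.50 | 0.138 | 78% | 0.46 |
| One visit, change | 0.7 | 0.60 | 0.151 | 70% | 0.51 |
| One visit, adjusted | 0.7 | 0.51 | 0.139 | 77% | 0.47 |
| Both visits, change | 0.7 | 0.45 | 0.130 | 82% | 0.44 |
| Both visits, adjusted | 0.7 | 0.36 | 0.117 | 89% | 0.39 |

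The df allowance matters by itself: the first row is 64% by the normal approximation and 49% on 6 df.

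**5. The same model at f = 0.25 (1.06 SD).** Power is at least 99% at ICC 0.02, r = 0.5.

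**6. Larger ICC (assumed).** At 0.05 the inflation is 1 + 16.6 × 0.05 = 1.83. One-visit power for 0.45 SD is then 38–48% at r = 0.5 and 57–64% at r = 0.7. At 0.10 it is 28–36% and 43–49%.

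**The case against.** The strongest defence is that the section promises 80% power for f = 0.25 and nothing else. The benchmarks come first, the meta-analysis is offered only as an example in support, and no conversion is claimed. For f = 0.25 the plan is more than adequate. This stands, so a reader should not infer that the stated 80% is false on its own terms.

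Three other strong readings are tempting and also fail:

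- **That clustering is ignored.** It is not: the ICC, the design effect and the eight classes are all in the calculation, and the analysis models class. Only the few-cluster df is missing.
- **That the trial is close to a coin-toss for 0.45 SD.** The 49% belongs to one visit, a change score, r = 0.5 and full dropout. The planned models use all three visits. With both later visits, baseline adjustment and no dropout, power at r = 0.5 is 84%.
- **That ICC 0.02 is wrong.** Data analysis does call variation between teachers unavoidable, but in the same sentence notes standardised course content, and 0.02 is attributed to sources not at hand. By the protocol's formula, 176 covers its stated minimum up to an ICC of (176/70 − 1)/21 = 0.072.

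The planned 95% confidence intervals would also show what a null result leaves open. None of this rescues the conservative label: even the most favourable conversion, 0.225, is below the f entered.

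**Conclusion.** The point holds in limited form. The cited SMD does not support f = 0.25, let alone as a conservative choice: it is 0.225 between groups and about 0.106 as the interaction, and f = 0.25 is about 1.06 SD, more than twice the cited effect. The 80% power is met for f = 0.25 but not established for SMD 0.45, and the sizing lacks an allowance for about 6 df.

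At the protocol's own ICC and dropout, on 6 df, power for 0.45 SD is 49–61% for one later visit and 61–78% for the mean of both at r = 0.5; at r = 0.7 it is 70–77% and 82–89%. Both correlations are assumptions, because the protocol gives none. The shortfall is therefore likely but not certain. The claim that 176 exceeds the requirement is right for f = 0.25 and unproven for the effect cited.

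**What to change.** In Sample size calculation:

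- Remove the statement that an SMD of 0.45 makes f = 0.25 conservative and realistic. If f = 0.25 is kept, say what it means in SD units at the later visits.
- State the between-visit correlation assumed, and whether 28 was a total or a per-group figure.
- Limit the statement that 176 exceeds the adjusted minimum to f = 0.25.
- Give the power and detectable difference of the fixed eight-class design for the trial's own planned contrast, with class-level df and expected dropout, at ICC 0.02 and at larger values labelled as assumptions (for example 0.05 and 0.10).
- Add that a null result may not exclude an SMD of 0.45.

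This changes wording and adds a short table. Recruitment, design and analysis stay as they are. The cost is a less favourable stated power.

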### Eligibility criteria and recruitment

Eligible participants must be first-year students enrolled in the required tennis PE course, aged 18 or above, and free from any disabilities, injuries, or illnesses that would impair their ability to perform daily tasks. Students with a regular habit of playing *TopSpin 2K25* will be excluded.

This study is scheduled to begin in the first week of the second semester of the 2025–2026 academic year in CUHK. A briefing session and participant recruitment will be conducted during the week of 5 January 2026, integrated into the schedule tennis PE lessons. Recruitment will conclude on 16 January 2026, coinciding with the end of the university’s add-drop period, at which point the class lists will be finalized. Recruitment will take place during the first lesson in the PE tennis courses, where teachers will explain the study and distribute consent forms. An introductory meeting will be held with the teachers to outline the intervention procedures and assessment methods. Additionally, a training workshop will be provided for research assistants and student helpers, covering gameplay instructions and guidelines for facilitating the gaming sessions.

### Randomization

Each semester, CUHK offers seven male and seven female tennis PE classes, all taught by different teachers but following standardized content and assessments. For this study, simple randomization will be used. Four male and four female entire classes will be randomly selected by drawing lots. Among these, two male and two female entire classes will be further randomly assigned to the intervention group using the same method.

### Intervention

A six-week tennis-themed SVG intervention will be implemented for participants in the intervention group, supplementing their regular tennis PE lessons. This intervention is designed to align with the study’s goals of promoting PL and enhancing physical activity engagement among university students in Hong Kong.

A dedicated **“SVG Corner”** will be set up in a classroom, equipped with two PlayStation 5 consoles, each connected to four controllers and a monitor. Participants will engage with the tennis-themed SVG ‘*TopSpin 2K25’*, released in April 2024, which is known for its highly realistic gameplay, including accurate physics, player movement, and court dynamics. This realism helps bridge the gap between virtual and physical tennis, making it a suitable tool for reinforcing PL concepts such as spatial awareness, timing, and movement strategies. The game includes tutorials and skill challenges that provide structured learning opportunities aligned with specific PL goals. For example:

1. **Physical Competence**:

Gameplay requires fast reaction time and eye-hand coordination, simulating real tennis movements and decision-making. These elements promote motor skill development, agility, and movement control, which are core aspects of physical competence.

2. **Motivation**:

The immersive and gamified nature of *TopSpin 2K25* enhances enjoyment and engagement. By offering a fun and competitive environment, the intervention aims to boost students’ overall interest and motivation in real-life sports, supporting long-term physical activity participation.

3. **Knowledge and Understanding**:

In-game tutorials and challenges help students understand tennis rules, tactics, and movement principles, reinforcing cognitive engagement with physical activity.

4. **Social Interaction**:

Multiplayer modes (singles and doubles) promote peer interaction, cooperation, and friendly competition, which are important social dimensions of PL.

To support accessibility and adherence, at least one research assistant or student helper will be present during operating hours to manage the SVG Corner and assist participants. Clear and concise control guidelines will be displayed in the SVG Corner for easy reference. To maintain the integrity of the intervention, no formal tennis instruction will be provided during gaming sessions.

Each participant in the intervention group will be required to attend two 20-minute gaming sessions per week, in addition to their regular PE classes. The SVG Corner will be open Monday to Friday, from 10:00–13:00 and 14:00–18:00. Due to equipment limitations (2 consoles with a total of 8 controllers), each session has limited quota. If a session reaches its quota due to the first-come-first-served arrangement, we will arrange an alternative time slot to accommodate affected participants. The attendance will be tracked weekly, in case where participants are unable to fulfill the attendance requirement, we will contact them via email to arrange make-up sessions. This ensures that all participants can fulfill the attendance requirement and receive the full intended dosage of the intervention.

To minimize contamination bias, students in the control group will not be provided access to the SVG Corner and will be advised not to engage in tennis-themed sports video gaming independently during the study period. While we cannot fully restrict external gaming behavior, participants will be informed of the importance of maintaining their assigned condition and asked to report any SVG-related activity outside the study. This will help us monitor potential crossover and account for it in the final analysis.

The first two sessions will include guided tutorials within the game to help participants become familiar with the controller layout and basic tennis concepts. For example, the initial tutorial focuses on repositioning, requiring players to return to the center area behind the baseline after each shot. An instructional video will explain the importance of repositioning and demonstrate how to control the avatar. Participants must successfully complete six repositioning tasks to move forward. From the third session onward, participants will engage in both singles and doubles matches, playing with or against other participants. No gaming sessions will be provided to the control group. Participants may withdraw from the intervention if they experience scheduling conflicts, physical discomfort, musculoskeletal or cardiovascular conditions, or are unable to comply with the intervention protocol. To support adherence, PE teachers and research assistants will regularly remind participants to attend their gaming sessions. Additionally, all participants in the intervention and control groups will receive four participation marks in their PE course upon completing the study.

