### Data analysis

Descriptive statistics, including means and standard deviations, will be calculated for university students’ video gaming time, gaming frequency, physical activity levels, physical literacy, reaction time, and eye-hand coordination across all relevant subscales and instruments. To examine baseline differences between groups in the cross-sectional study, one-way analyses of variance (ANOVAs) will be conducted.

To evaluate intervention effects, mixed-effects models will be employed instead of simple repeated-measures ANOVAs to account for the hierarchical structure of the data and potential intra-cluster correlation among participants within the same class group. This approach addresses the reality that, although courses follow standardized content, variability in teaching style, instructor enthusiasm, and informal reinforcement of the intervention is inevitable in real-world PE settings. Mixed-effects models will include fixed effects for time (baseline, post-intervention, follow-up) and group (intervention vs. control), as well as random effects for class clusters to capture variability across different teaching contexts. These models will assess both main effects and interaction effects, providing more accurate standard error estimation and valid statistical inference.

For secondary outcomes (motivation, cognitive knowledge, social engagement, and physical activity), similar mixed-effects or generalized estimating equation models will be applied, depending on distributional assumptions. Multiple linear regression analyses will explore predictive relationships between PL and physical activity levels, with SVG gaming included as a potential mediator or moderator. Covariates such as baseline physical activity, prior SVG experience, and demographic characteristics (age, gender) will be adjusted for in all models. Interaction effects between the intervention and participant characteristics (e.g., gender, gaming experience) will also be examined to identify subgroup differences.

To enhance the interpretability and transparency of our findings, partial eta-squared will be reported for all primary outcomes to indicate the magnitude of observed effects. Additionally, 95% confidence intervals will be provided to reflect the precision of the estimates and the range within which the true effect is likely to fall. These metrics will support a more nuanced understanding of the intervention’s impact and facilitate comparison with other studies.

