### Patient and public involvement

Students were not involved in the initial design of this study. Both students and teachers will participate in the conduct, reporting, and dissemination phases. Teachers from the tennis classes involved in the study contributed to its design and will continue to be engaged through regular meetings to provide feedback and insights as the study progresses.

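### Teacher reinforcement confined to intervention classes is confounded with the effect of the game, and the class random effect does not address it

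*Protocol article*

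**What the plan says.** Study design sets the contrast: what playing the tennis game achieves over and above the usual tennis classes.

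The Intervention section gives teachers a recurring task: "To support adherence, PE teachers and research assistants will regularly remind participants to attend their gaming sessions". The same section adds "No gaming sessions will be provided to the control group", so the task can exist in one arm only.

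Randomization describes the classes as "all taught by different teachers but following standardized content and assessments". Each teacher therefore belongs to a single class and a single arm.

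Teachers are informed about the trial. Eligibility criteria and recruitment says "An introductory meeting will be held with the teachers to outline the intervention procedures and assessment methods", and Patient and public involvement says "Teachers from the tennis classes involved in the study contributed to its design and will continue to be engaged through regular meetings". No blinding of teachers is stated, and a teacher who reminds students of gaming sessions knows the allocation.

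On the mixed model, Data analysis says "This approach addresses the reality that, although courses follow standardized content, variability in teaching style, instructor enthusiasm, and informal reinforcement of the intervention is inevitable". The term meant to achieve this is described "as well as random effects for class clusters to capture variability across different teaching contexts".

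**The concern.** In a comparison of game plus PE with PE alone, whatever the teacher does should be alike in both arms if the difference is to be credited to the game. Here one teacher activity is planned for one arm, and a further one, informal reinforcement, is accepted as unavoidable. Reinforcement of an intervention by a class's own teacher is to be expected only where the class receives that intervention.

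The Data analysis section treats this as a nuisance that the model takes care of. If that is not so, a gain in motivation, tennis knowledge, social engagement or physical activity could come partly from the teacher's attention and be reported as an effect of the game, with the analysis cited as the safeguard.

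**Working it through.** The article gives no figure for teacher reinforcement, so there is none to reproduce. The check is whether a class random effect can remove a shift that follows the arm.

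**Inputs from the article.** 8 classes, 4 per arm, 22 students each (Study design); ICC 0.02 (Sample size calculation). ICCs of 0.05 and 0.10 were added as a range.

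**Assumed inputs.** Outcome SD 1, true game effect 0, and an average teacher shift b in intervention classes only. The values of b are assumptions. The largest, 0.45, is set equal to the SMD that the article cites from a meta-analysis of exergame trials.

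**Algebra.** Take one post-baseline contrast per student, standing for the group-by-time effect at one visit. For class j, with a = 1 for intervention and 0 for control, the class mean is

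mean_j = μ + a·(γ + b + d_j) + u_j + e_j

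Here γ is the game effect, b the average teacher shift, d_j the departure of teacher j from that average, u_j the class effect and e_j the averaged student error. The expected difference between arms is γ + b. The random effect takes up u_j and d_j, which scatter around the arm mean. It cannot take up b, because b is the same as a change in the arm mean. Baseline adjustment does not remove b either, since reinforcement begins after baseline.

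**Precision at ICC 0.02.** SE = √[(2/4) × (0.02 + 0.98/22)] = √(0.5 × 0.0645) = 0.18 SD, on 6 degrees of freedom.

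**Simulation** (20,000 trials per cell, class-level analysis equivalent to a class random intercept in this balanced design, γ = 0):

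| Assumed b (SD) | Mean estimate, ICC 0.02 | p < 0.05, ICC 0.02 | p < 0.05, ICC 0.05 | p < 0.05, ICC 0.10 |
|---|---|---|---|---|
| 0 | 0.00 | 4.6% | 5.4% | 5.2% |
| 0.1 | 0.10 | 7.9% | 6.6% | 6.2% |
| 0.2 | 0.20 | 15.8% | 12.3% | 9.7% |
| 0.3 | 0.30 | 29.3% | 21.4% | 16.0% |
| 0.45 | 0.45 | 55.7% | 41.9% | 30.3% |

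**Fitted mixed model** (REML, 150 trials, b = 0.2, ICC 0.02). The mean estimate was 0.19 (simulation SE 0.014). The estimated class variance was 0.024 with the shift and 0.022 without it, so the random effect did not absorb the shift.

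**Shift varying by teacher** (uniform from 0 to twice its mean, 300 trials per case, fitted class random intercept). Mean shifts of 0.1, 0.2 and 0.3 gave mean estimates of 0.093, 0.194 and 0.322 (simulation SE about 0.011). Variation between teachers does not change the result.

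**The case against.** The strongest reply is that a routine attendance reminder is being read as a difference in teaching. A reader might infer that teachers are told to promote the game inside PE lessons, and that lessons therefore differ systematically by arm. The article supports neither. It speaks of reminding students to attend and does not say where this happens. Content and assessments are standardized, and the gaming takes place outside scheduled class time.

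Data analysis can also be read narrowly. Its subject is variability, and the benefits it names include more accurate standard errors, which is what a class random effect provides. It never mentions the planned reminders and never says in so many words that a shift common to one arm is removed. This stands against calling the whole paragraph false. It does not rescue the wording, because the list of things the approach is said to deal with includes informal reinforcement, and for its average in intervention classes that is not correct.

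The simulation returns the shift that was put in, and nothing in the article suggests how large a shift a reminder would cause. That is right. The table shows that the shift passes through in full, not that a shift of any given size will occur.

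Adherence support can also be regarded as part of the intervention. The estimate is then valid for the package, and what remains is a limit on crediting the game alone. That limit matters because the Introduction links the expected gains to particular game mechanics.

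Limitations does mention teaching style and the Hawthorne effect. It treats teaching differences as a matter of consistent delivery, not as a difference between arms.

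**Conclusion.** The point holds in a limited form. Teacher reminders are specific to the intervention arm, teacher is nested in class and class in arm, and the article itself expects informal reinforcement. Any average reinforcement confined to intervention classes is wholly confounded with the group-by-time effect. The class random effect handles only scatter between classes within arms, so Data analysis credits it with too much.

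Full pass-through of the shift does not depend on its size, but the practical importance does, and that size is unknown. At ICC 0.02 an assumed shift of 0.1 SD barely changes the rate of p < 0.05 (7.9% against 4.6%), while 0.3 SD brings it to 29.3%. It remains a risk, not a documented fact, that lessons differ between arms. It bears mainly on the outcomes that Data analysis calls secondary: motivation, knowledge, social engagement and physical activity. No clear route leads from a reminder to the ruler-drop or wall-toss results.

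**What to change.** 1. At the introductory teacher meeting already planned, ask teachers in both arms to keep lesson content the same and not to link lessons to the game up to the Week 11 follow-up. Exempt their adverse-event duties under Harms.
2. Send attendance reminders through research assistants and the email route already used to arrange make-up sessions, and take PE teachers out of the reminder sentence. Reminders would still go to one arm only, but no longer from the person who teaches the class.
3. In Data analysis, state that the class random effect accounts for between-class variation and for standard errors only. Add that any teacher reinforcement common to intervention classes is part of the estimated effect, so the estimate describes the delivered package and not the game alone.

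The cost is some rewording and one agenda item. Attendance may fall slightly without teacher reminders; by how much is not known, but weekly tracking and make-up sessions are already in place to limit it. If the teacher reminders are kept for adherence, the third change is still needed.
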